## Results

A total of 32 schools from four geographical regions in New South Wales tendered an Expression of Interest for the study to the NSW Department of Education and Training and were assessed for eligibility. The four regions, outer Sydney metropolitan, Illawarra and South Coast, Hunter and New England, and the North Coast incorporated a range of socio-economic, urban and rural settings. From the original 32 schools, 8 were unable to be matched based on the *a priori *criteria, leaving 24 that were matched and randomly allocated to the intervention or control group. One of the schools withdrew after being allocated to the control group and was replaced with another school that was nominated by the NSW Department of Education and Training as a suitable school to be matched to the intervention school. The flow of schools and individual students through the enrolment and allocation stages of the study are displayed in Figure 1. Eighty-six percent of eligible girls completed baseline assessments, 771 in the intervention group and 747 in the control group. Table 2 shows the baseline characteristics of participants on demographic, outcome and mediator/moderator variables.

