**Methods/Design:**

A community-based participatory research approach and action learning framework are used with measurements at baseline and 18-month follow-up. Within each intervention school, a committee develops an action plan aimed at meeting the primary objective (preventing the decline in accelerometer-derived MVPA). Academic partners and the State Department of Education and Training act as critical friends. Control schools continue with their usual school programming. 24 schools were matched then randomized into intervention (n = 12) and control (n = 12) groups. A total of 1518 girls (771 intervention and 747 control) completed baseline assessments (86% response rate). Useable accelerometer data (≥10 hrs/day on at least 3 days) were obtained from 79% of this sample (n = 1199). Randomisation resulted in no differences between intervention and control groups on any of the outcomes. The mean age (SE) of the sample was 13.6 (± 0.02) years and they spent less than 5% of their waking hours in MVPA (4.85 ± 0.06).

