## Methods/Design

The study was funded by the New South Wales (NSW) Department of Education and Training (who are responsible for all government schools) through a competitive tender process and is registered with the Australian New Zealand Clinical Trials Registry (ACTRN12610001077055). The University of Wollongong Human Research Ethics Committee approved the study protocol (HE08/296).

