### Randomization and study design

This was a group randomized controlled trial with school as the unit of randomization. Each matched pair of schools was randomly allocated to the intervention or control group using a computer-based random number producing algorithm. This was undertaken by a researcher independent of the project and then communicated to the research team who informed each school of its allocation. Due to the timeframe of the study, formative research was required to be conducted in the intervention schools in Term 4 (October to December 2008). This meant randomization needed to occur prior to baseline data collection.

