### Inclusion and exclusion criteria

To be eligible for the study, schools were required to not be involved in any other physical activity-related research projects and to confirm that they consented to being randomized to either the intervention or control group if they were selected for the project. If selected in the intervention group, schools needed to commit to developing an action plan, forming a school committee, attending workshops, organizing students for data collection days and putting the project in the school management plan. Girls needed to be formally enrolled in Grade 8 within the participating schools and provided written consent from themselves and their parent(s)/guardian(s) prior to participation. If a student or their parent/guardian did not consent, they were still able to participate in the intervention activities but did not participate in data collection.

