Raw means are presented. Analysed intervention and control means and se are adjusted LS estimates from the PROC MIXED procedure in SAS V 9.2. The model used specifies randomisation group and pairing in the class statement as recommended by Murray [32]. Degrees of freedom are entered manually using the formula (randomisation groups-1)x(pairs-1) and in this study is equal to 11. Only those subjects who completed the specified questionnaire subdomains are included in this table with the numbers indicated in brackets (n). *accelerometer estimates include accelerometer type in the model.

We obtained useable accelerometry data from almost 80% of adolescent girls (79.1%). There were no statistically significant differences between the intervention and control groups on any of the variables. Although differences between the two groups approached statistical significance for three of the variables (percentage of time spent in light intensity physical activity, enjoyment of school sport, and social support for physical activity), from a clinical perspective they are not of any note. The sample demonstrated low levels of physical activity participation. Only 1.5% met current physical activity recommendations for adolescents of ≥60 minutes of MVPA every day [36]. Moreover, the girls spent 60% of their waking hours being sedentary and less than 5% in moderate-to-vigorous intensity physical activity (MVPA).

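### One control school was replaced after allocation by a nominated, non-randomised school; the abstract omits this, the baseline analysis counts 12 pairs, and no analysis is tied to the affected pair

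*Protocol article*

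**What the plan says.** Under Randomization and study design: "Each matched pair of schools was randomly allocated to the intervention or control group using a computer-based random number producing algorithm". A researcher independent of the project did this. Because formative work had to start in the intervention schools, "This meant randomization needed to occur prior to baseline data collection".

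Under Results, 24 of 32 interested schools were matched and randomised. One then "withdrew after being allocated to the control group and was replaced with another school that was nominated by the NSW Department of Education and Training", the substitute being described "as a suitable school to be matched to the intervention school". The Methods/Design section states: "The study was funded by the New South Wales (NSW) Department of Education and Training". Setting and population names a unit of the Department as a study partner, and the Intervention section says the Department gave funding to support the intervention schools.

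The abstract says only that "24 schools were matched then randomized into intervention (n = 12) and control (n = 12) groups", and it attributes the absence of baseline differences to randomisation. The notes under Table 2 say: "Degrees of freedom are entered manually using the formula (randomisation groups-1)x(pairs-1) and in this study is equal to 11". The Discussion mentions the withdrawal, links it to collecting baseline data after randomisation, and concludes from the baseline tests that no significant group differences resulted. Under Primary analyses, sensitivity analyses are promised in one short sentence after the missing-data text, with no stated content.

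**The concern.** The substitute did not pass through the random allocation described in the Methods. It was selected when the vacant place was known to be a control place and its partner was known to be an intervention school. The selecting body has an interest in the trial, whereas the allocation itself had been given to an independent researcher. One of the 12 pair differences behind the treatment contrast is therefore a chosen comparison. If the nominated school differs from the withdrawn one in ways related to the trend in girls' activity, the effect estimate carries that difference, and its direction cannot be told from the documents.

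Baseline tests do not settle this. They compare whole arms, so a distortion confined to one of 12 pairs is diluted. They also say nothing about unmeasured school features or about change over 18 months, which is what the primary aim concerns. A reader of the abstract alone would not learn that the question exists.

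**Working it through.** **Counting the schools.**
- Randomised: 24 (12 pairs).
- Randomised schools that stayed: 24 − 1 = 23.
- Added by nomination: 1.
- Schools supplying data: 23 + 1 = 24.
- Pairs with both members randomised and retained: 12 − 1 = 11.

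**Degrees of freedom.** The formula under Table 2 is (groups − 1) × (pairs − 1).
- With 12 pairs: (2 − 1)(12 − 1) = 11, the value stated, so the replaced pair is counted.
- With the 11 intact pairs: (2 − 1)(11 − 1) = 10, with two-sided 5% critical t of 2.228.

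**Possible bias.** With roughly equal pair weights, the treatment contrast is close to the mean of 12 pair differences. A bias b in one of them shifts it by b/12, about 8% of b. The documents give no basis for a value of b.

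**Reproducing the stated power.** Inputs from Sample size justification: effect 42.07 cpm, SD 102.92 cpm, intraclass correlation 0.01, m = 30 girls per school, g = 12 schools per group, critical t 2.228.
- The standard error in that section is √[2(σ²_m + mσ²_g)/(mg)]. With σ²_g = 0.01 × 102.92² and σ²_m = 0.99 × 102.92², it becomes 102.92 × √[2(0.99 + 30 × 0.01)/(30 × 12)] = 102.92 × √(2 × 1.29/360) = 8.71 cpm.
- 42.07/8.71 = 4.83, and 4.83 − 2.228 = 2.60.
- P(t with 10 df < 2.60) = 0.987, the stated figure.

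**Power without the affected pair.**
- SE = 102.92 × √(2 × 1.29/330) = 9.10 cpm.
- 42.07/9.10 = 4.62, and 4.62 − 2.228 = 2.39 before rounding the ratio.
- P(t with 10 df < 2.39) = 0.981.

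**Less favourable inputs.** Table 2 gives an SE of 3.79 for counts per minute in 1199 girls. Read as the simple standard error of a mean, this implies an SD of 3.79 × √1199 ≈ 131. The intraclass correlation of 0.05 is an assumption; the plan says it had no reliable estimate.

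| Inputs | 12 pairs | 11 pairs, 10 df |
|---|---|---|
| SD 102.92, ICC 0.01 | 0.987 (t 2.228) | 0.981 |
| SD 131, ICC 0.01 | 0.925 (t 2.228) | 0.904 |
| SD 102.92, ICC 0.05 | 0.890 (11 df, t 2.201) | 0.857 |
| SD 131, ICC 0.05 | 0.70 (11 df, t 2.201) | 0.65 |

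In the last row both analyses fall below 80%, so the shortfall there comes from the inputs and not from dropping the pair. All figures are for counts per minute, the outcome the plan powers. The primary outcome in Primary analyses is percentage of time in MVPA.

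**The case against.** The event is disclosed in the Results, and the abstract's sentence is literally true of the 24 schools originally drawn. One pair in 12 limits the damage, and measurement at baseline and follow-up would partly offset a stable difference in activity level. All of this stands. It bears on severity and does not remove the point.

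Three stronger readings are tempting, and the documents do not support them.

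- *The replacement was ineligible.* Schools had "to confirm that they consented to being randomized to either the intervention or control group if they were selected for the project". The article does not say whether the substitute gave that confirmation. Nor does it say where the school came from; it could have been one of the 8 interested schools that could not be matched. The flow diagram is not shown. What is known is that the school was not randomised.
- *The outcome analysis is fixed at 12 randomised pairs.* The 11 degrees of freedom belong to the baseline table. Primary analyses sets neither the pairs nor the degrees of freedom for the outcome model, and the content of the sensitivity analyses may lie in a fuller plan.
- *The 11 remaining pairs are a clean randomised trial and should be the primary set.* The Discussion ties the withdrawal to baseline collection after randomisation, so it may have depended on allocation. If so, a pair containing a school unwilling to be a control is lost when that school draws control and kept when it draws intervention. The 11 pairs would then be selected on a post-randomisation event. Excluding the pair also discards an intervention school that was properly randomised.

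**Conclusion.** The point holds as a should-fix. One of the 12 pairs was not formed by the trial's randomisation. The abstract does not say so, the baseline analysis counts the pair like the others, and the Discussion's reassurance does not follow from non-significant tests. The exposure is about one-twelfth of whatever bias that pair carries, assuming roughly equal weights; its size and direction are unknown. Checking it is cheap: about 0.6 points of power on the plan's own inputs, about 2 points at an SD of 131, and about 3 points at an assumed intraclass correlation of 0.05. The problem is one of validity and reporting, not of power. Neither the 12-pair nor the 11-pair set is guaranteed free of selection, which is why the two should be shown together.

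**What to change.** 1. In the abstract and under Randomization and study design, state that 24 schools were randomised and that one control school withdrew after allocation and was replaced by a non-randomised school nominated by the Department. Add where the replacement came from, whether it met the matching criteria, and whether it had agreed to either arm.
2. Remove the inference that non-significant baseline tests show the withdrawal and replacement did no harm.
3. Before outcomes are analysed, specify a sensitivity analysis of the primary outcome that excludes the affected pair (11 pairs, 10 degrees of freedom, critical t 2.228). Report it beside the 12-pair result with estimates and confidence intervals, and qualify any efficacy claim if the two disagree.

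The cost is a few sentences and one more model run, with the small loss of power shown above confined to the sensitivity analysis. The 12-pair analysis can remain primary.

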**Figure 1 F1:**
[figure not shown]
**Flow of schools and participants through the trial**.

**Table 2 T2:** Baseline demographic characteristics and outcome measures of *Girls in Sport *participants

	Intervention Group(1)	Control Group(0)	P	All
Age in years, mean (SE)	13.71 ± 0.04	13.48 ± 0.02	0.3512	13.60 ± 0.02
Physical activity* (n = 1199)				
Counts per minute, mean (SE)	428.40 ± 5.50	418.44 ± 5.22	0.2367	423.14 ± 3.79
Percentage time sedentary intensity	60.07 ± 0.32	61.22 ± 0.28	0.1210	60.83 ± 0.21
Percentage time light intensity	34.95 ± 0.27	33.95 ± 0.24	0.0655	34.26 ± 0.19
Percentage time moderate intensity	4.51 ± 0.08	4.32 ± 0.08	0.1482	4.38 ± 0.06
Percentage time vigorous intensity	0.455 ± 0.02	0.512 ± 0.02	0.6826	0.476 ± 0.01
Percentage time moderate-to-vigorous activity	4.97 ± 0.09	4.83 ± 0.09	0.3184	4.86 ± 0.06
Percentage of participants meeting recommended 60 mins of MVPA every day	1.9	1.1	0.253	1.5
Percentage of participants meeting recommended 60 mins of MVPA per day on average	10.6	9.6	0.682	10.1
Physical self-worth (n = 1467)	16.04 ± 0.14	16.40 ± 0.14	0.1798	16.22 ± 0.10
Sports competence (n = 1465)	15.42 ± 0.14	15.70 ± 0.13	0.2739	15.56 ± 0.10
Physical condition (n = 1468)	16.04 ± 0.14	16.38 ± 0.14	0.1389	16.21 ± 0.10
Body attractiveness (n = 1462)	14.02 ± 0.14	14.39 ± 0.15	0.2748	14.21 ± 0.10
Physical strength (n = 1461)	15.09 ± 0.13	15.35 ± 0.12	0.2002	15.22 ± 0.09
Physical activity confidence (n = 1510)	29.74 ± 0.16	29.88 ± 0.17	0.4675	29.81 ± 0.12
Enjoyment of physical activity (n = 1503)	29.77 ± 0.16	29.63 ± 0.16	0.5504	29.70 ± 0.12
Enjoyment of school sport (n = 1510)	28.06 ± 0.19	27.40 ± 0.20	0.0641	27.74 ± 0.14
Social support for physical activity (n = 1510)	12.54 ± 0.10	12.02 ± 0.11	0.0768	12.29 ± 0.08
Social support during school sport (n = 1503)	23.83 ± 0.16	23.65 ± 0.16	0.6594	23.75 ± 0.11
Strategies to increase physical activity (n = 1509)	25.32 ± 0.18	24.93 ± 0.19	0.3935	25.13 ± 0.13
School physical activity environment (n = 1508)	26.26 ± 0.16	25.88 ± 0.16	0.6952	26.07 ± 0.11
Perceived importance of physical activity (n = 1459)	22.42 ± 0.15	22.39 ± 0.15	0.8685	22.41 ± 0.11

Raw means are presented. Analysed intervention and control means and se are adjusted LS estimates from the PROC MIXED procedure in SAS V 9.2. The model used specifies randomisation group and pairing in the class statement as recommended by Murray [32]. Degrees of freedom are entered manually using the formula (randomisation groups-1)x(pairs-1) and in this study is equal to 11. Only those subjects who completed the specified questionnaire subdomains are included in this table with the numbers indicated in brackets (n). *accelerometer estimates include accelerometer type in the model.

We obtained useable accelerometry data from almost 80% of adolescent girls (79.1%). There were no statistically significant differences between the intervention and control groups on any of the variables. Although differences between the two groups approached statistical significance for three of the variables (percentage of time spent in light intensity physical activity, enjoyment of school sport, and social support for physical activity), from a clinical perspective they are not of any note. The sample demonstrated low levels of physical activity participation. Only 1.5% met current physical activity recommendations for adolescents of ≥60 minutes of MVPA every day [36]. Moreover, the girls spent 60% of their waking hours being sedentary and less than 5% in moderate-to-vigorous intensity physical activity (MVPA).

## Discussion

*Girls in Sport *is a group randomized trial which aims to test the effectiveness of an intervention developed by each school and that simultaneously targets school sport, environment and policy changes, and community links, to prevent a decline in MVPA among adolescent girls. Detailed formative research has guided the action plans developed by each school and these have been externally evaluated by the research team. Progression on these action plans is regularly maintained during the intervention through ongoing contact between school staff, the research team, and the NSW Department of Education and Training. As this is one of the first known school-based interventions to promote physical activity that has used a community-based participatory research approach and action learning framework, it is hoped the lessons learnt can inform others who are developing similar studies in the future.

To achieve acceptable response rates within each school (all >80% with many exceeding 90%) staff members of the school committee encouraged girls to return their consent forms and followed up any that were outstanding. Because these staff had a good rapport with the girls (many taught the girls or were their Year Advisor) they were able to explain in detail the study and what changes may result for these girls. Because the intervention involved all girls in the specific grade, there was no stigma associated with being involved.

Staff were also able to encourage girls to wear the accelerometer (many staff also wore them to enhance compliance) and stress the importance of keeping them on outside of school hours. Again, involving all girls reduced any stigma associated with others seeing the monitors. Schools were also encouraged to pay for release time for staff so they could organise the assessment times and locations for each class, chase up outstanding consent forms, and schedule interview times for girls and staff. This meant staff had time to devote to this and were not having to complete it on top of their other teaching and school commitments. Collecting the questionnaire data over two visits, one week apart, allowed the research team to collect the accelerometers on the second visit and also obtain any missing data from the first visit. Training school staff in how to show the girls the correct way to wear the monitor meant that they could distribute these to any girls who were absent during data collection. Conducting the questionnaires in a classroom with individual desks and away from other students (especially boys) facilitated quality data (less than 5% missing or completed incorrectly) as girls could feel assured that their responses would be treated confidentially.

There were no significant differences between groups at baseline for any of the variables. This shows that the matching of schools on demographic and other school-related factors prior to randomisation was successful and that collecting the baseline data after randomisation (which resulted in one school allocated to the control group withdrawing) did not result in any significant differences between groups. The matching of schools is an important and potentially effective way of maximising the chance of the groups being similar at the start of the intervention, minimising several potential threats to the internal validity of the study, especially differential threats [32].

Accelerometer data highlighted that girls spent 60% of their waking hours sedentary and only 5% in MVPA. These proportions are similar for both variables to those reported among a similar sample of 12-year-old girls as part of baseline measures for the TAAG study (55% sedentary and 3% MVPA, respectively) [37]. With regards to the raw accelerometry data (expressed as counts per minute), our value of 423.43 is similar to that reported for 12-15 year old adolescent girls in the NHANES study (381.60) [3].

This study will provide an opportunity to test a variety of mediators and moderators of physical activity behaviour. Few studies have assessed mediators of physical activity behaviour in youth interventions and this study will help provide insights into the mechanisms of behaviour change in a large sample of adolescent girls [38]. In addition, the majority of studies that explored potential mediators of intervention effects in youth have used self-report measures of physical activity. To the authors' knowledge only two studies have examined mediators in youth interventions using an objective measure of activity [39,40].

The development of positive physical self-perceptions may provide the foundation for future physical activity [41]. Previous studies have illustrated the importance of physical self-perceptions in explaining adolescents' physical activity behavior [42]. Adolescents' physical self-perceptions have been found to predict physical activity in longitudinal studies [43] and improve as a result of increased activity [44]. In the current study we will test the mediating and moderating effects of physical self-perception on physical activity.

## Conclusions

The *Girls in Sport *intervention is unique in that individual schools are primarily responsible for developing and implementing the intervention. By giving schools ownership of the intervention and the opportunity to develop strategies which meet the specific needs, interests and expertise within schools, it is hoped that these programs become embedded into the school culture, maximising their sustainability beyond the life of this evaluation project. It is also hoped that by each school forming a committee that includes at least one executive staff member, several staff from different faculty, and students, that the workload and responsibility is shared among the committee, again enhancing sustainability when staff (and students) move from the school.
